## Abstract

**Background:**

To support the use of research evidence by community-based organizations (CBOs) we have developed 'Synthesized HIV/AIDS Research Evidence' (SHARE), which is an evidence service for those working in the HIV sector. SHARE consists of several components: an online searchable database of HIV-relevant systematic reviews (retrievable based on a taxonomy of topics related to HIV/AIDS and open text search); periodic email updates; access to user-friendly summaries; and peer relevance assessments. Our objective is to evaluate whether this 'full serve' evidence service increases the use of research evidence by CBOs as compared to a 'self-serve' evidence service.

**Methods/design:**

We will conduct a two-arm randomized controlled trial (RCT), along with a follow-up qualitative process study to explore the findings in greater depth. All CBOs affiliated with Canadian AIDS Society (n = 120) will be invited to participate and will be randomized to receive either the 'full-serve' version of SHARE or the 'self-serve' version (a listing of relevant systematic reviews with links to records on PubMed and worksheets that help CBOs find and use research evidence) using a simple randomized design. All management and staff from each organization will be provided access to the version of SHARE that their organization is allocated to. The trial duration will be 10 months (two-month baseline period, six-month intervention period, and two month crossover period), the primary outcome measure will be the mean number of logins/month/organization (averaged across the number of users from each organization) between baseline and the end of the intervention period. The secondary outcome will be intention to use research evidence as measured by a survey administered to one key decision maker from each organization. For the qualitative study, one key organizational decision maker from 15 organizations in each trial arm (n = 30) will be purposively sampled. One-on-one semi-structured interviews will be conducted by telephone on their views about and their experiences with the evidence service they received, how helpful it was in their work, why it was helpful (or not helpful), what aspects were most and least helpful and why, and recommendations for next steps.

**Discussion:**

To our knowledge, this will be the first RCT to evaluate the effects of an evidence service specifically designed to support CBOs in finding and using research evidence.

**Trial registration:**

ClinicalTrials.gov: NCT01257724

## Background

Community-based organizations (CBOs) are important stakeholders in health systems [1,2] because they provide a wide spectrum of programs and services to the members of their community, link with other health and social services to help provide care, and advocate for broader system-level supports. As with other health system stakeholders (*e.g.*, healthcare providers and health system managers and policymakers) it is important for CBOs to use research evidence to inform their programs, services and advocacy. To do this, they need support in finding and using research evidence to help them plan and deliver more effective and cost-effective programs and strengthen health systems.

However, there are many potential challenges related to research use. Barriers that have been consistently identified across different sectors include the complexity of research evidence, organizational barriers, lack of available time, poor access to current literature, lack of timely research, lack of experience and skills for critical appraisal, unsupportive culture for research, lack of actionable messages in research reports, and limited resources for implementation [3-7]. Given these barriers, it is not surprising that, generally, a lack of uptake of research evidence has been noted in many different sectors [8-12].

While there are strategies for supporting the use of research evidence by clinicians [13,14], and health system managers and policymakers [15-20], there is still an important gap in the availability of specific strategies for CBOs [21]. Many existing strategies for supporting the use of research evidence are based on experience and anecdotal evidence rather than on rigorous evidence of effects [15,22,23]. Moreover, strategies designed for supporting the use of research evidence by healthcare organizations and governments may not be relevant to the specific contexts and capacity of CBOs. To begin to fill this gap, we have developed an evidence service which for those working in the HIV sector, which is entitled 'Synthesized HIV/AIDS Research Evidence' (SHARE -- see below for a detailed description).

Efforts to facilitate the use of research evidence often focus on four clusters of knowledge translation activities ('producer push,' facilitating 'user pull,' 'user pull,' and 'exchange' efforts) [24], and the SHARE database primarily fits within two of these strategies. First, SHARE constitutes an effort to facilitate 'user pull' by allowing users to easily identify relevant synthesized research evidence and access user-friendly summaries when they identify the need for it. In addition, SHARE also constitutes a 'producer push' effort by providing periodic email updates that highlight synthesized research evidence that has been newly added to the database. This type of activity largely promotes awareness of newly synthesized research evidence, but it could also have more direct impact on the use of synthesized research evidence by profiling systematic reviews that address issues that CBOs may be grappling with at a particular time. What SHARE does not include are 'user pull' mechanisms (*i.e.*, target audiences incorporating prompts for research evidence in their decision-making processes and developing their capacity to find and use research evidence) or 'exchange' efforts, which focus on the producers and users of researchers building partnerships and working collaboratively in the production and interpretation of research evidence [24].

## Objectives

Our objective is to evaluate whether, how, and why this 'full serve' evidence service increases the use research evidence by key decision makers in CBOs as compared to a 'self-serve' evidence service.

## Methods/design

We will conduct this trial using a sequential explanatory mixed methods design [25], beginning with the two-arm randomized controlled trial (RCT), and then following up with a qualitative process study to explore the RCT findings in greater depth. The trial will run for 10 months, which includes a two-month baseline period where all participants receive the 'self-serve' evidence service, a six-month period where the intervention group will receive the 'full-serve' evidence service and the control group will continue to receive the 'self-serve' evidence service, and a final two-month period where both groups will receive the 'full-serve' version of SHARE.

## RCT methods and design

### Study population and recruitment

Community-based HIV/AIDS organizations in Canada provide a number of programs and services to people living with or affected by HIV, which may include prevention initiatives, individual or group counseling/support, and community outreach and/or education. In addition, organizations in Canada are situated in diverse geographic settings ranging from dense urban settings to rural, northern, and/or remote settings, with some focused on specific at-risk populations and/or cultural or ethnic groups.

We will draw our sample from those organizations affiliated with the Canadian AIDS Society and from relevant provincial HIV/AIDS networks (*e.g.*, the Ontario AIDS Network), and send an organizational invitation to the executive director and management team (if applicable). The invitation will indicate that if they are interested in having their organization participate, access to SHARE will be provided to all interested staff. Given that SHARE is currently only provided in English, we will exclude organizations that do not have at least one key decision maker who is comfortable participating and corresponding in English.

To ensure clarity in our study recruitment, we will outline that consent from the executive director is required for the organization to participate. We will also indicate that we require one key organizational decision maker to fill out a brief survey measuring their intention to use research evidence (see the Outcomes section for more detail on the survey) on behalf of their organization at baseline and again at the completion of the trial. We will request that the executive director complete the survey, but will indicate that they can delegate to another manager provided the manager has a decision-making role about programs, services, and advocacy, and provided the manager does not include the conduct of research among their core responsibilities. Because the overall intent of the intervention is to support the use of research evidence in decisions about CBOs' programs, services, and advocacy, we deemed it most appropriate for the executive director (or another manager) to complete the survey because they would have the most impact on whether research evidence is used to inform decisions.

Based on the membership list provided by the Canadian AIDS Society on their website, there are 120 CBOs available to draw the sample from. Drawing on previous experience with this sector, we expect to achieve an approximate response rate of 70%. To increase our response rate, the Canadian AIDS Society will send out an email to all its members, encouraging them to participate by highlighting the importance of the trial. We will provide additional incentive to enroll in the trial by holding a draw where we will select three organizations to receive prizes (gift cards) worth $500, $250 and $100.

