Using a manual to support health researchers who want to construct measures based on the theory [41], our colleagues have developed and sought preliminary feedback on a data-collection instrument by first assessing face validity through interviews with key informants and then pilot testing it with 28 policymakers and researchers from 20 low- and middle-income countries who completed it after participating in a KT intervention [48]. In addition, Boyko *et al*. (2010) found moderate test-retest reliability of the instrument using Generalizability Theory (G = 0.50) [49] when scores from a sample of 37 health system policymakers, managers, professionals, citizens/consumers, and researchers participating in stakeholder dialogues convened by the McMaster Health Forum were generalized across a single administration, and even stronger reliability (G = 0.9) when scores were generalized across the average of two administrations of the tool [48]. In the reliability assessment by Boyko *et al*. (2010), the first administration of the tool immediately followed a McMaster Health Forum stakeholder dialogue, which may have promoted enthusiasm for using research evidence among participants. This likely produced higher measures of intention on the first administration of the tool as compared to the second, resulting in the lower G-score. Given that we won't be administering the tool in a similar atmosphere of enthusiasm for using research evidence, it is likely that the level of reliability of the tool will be sufficient without two administrations at both baseline and follow-up.

We have slightly modified the wording in each of the questions of the tool to reflect the different intervention being tested (SHARE) and the target audience (CBOs) (see Additional file 3: Appendix 3). We will administer the instrument to one key decision maker from each organization during the baseline period, as well as at the end of the six-month intervention period, through a brief online survey that takes approximately 10 minutes to complete. We will use unique identifiers for each participant to ensure their responses to the previous survey are linked for calculations of before-and-after changes in their intention to use research evidence. We will follow up with participants who do not complete the survey once per week for three weeks to minimize the number of participants lost to follow up.

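### The follow-up intention survey is given two dates, one on each side of the control arm's switch to full-serve, and the two must be reconciled

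*Protocol article*

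**What the plan says.** All references are to the protocol article.

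- **Study population and recruitment.** Organizations will be told that a decision maker must fill in the intention survey "on behalf of their organization at baseline and again at the completion of the trial". The same sentence refers the reader to the Outcomes section for detail on the survey.
- **Outcomes (text after Figure 1).** The instrument is given "during the baseline period, as well as at the end of the six-month intervention period, through a brief online survey". People who have not answered are then contacted "once per week for three weeks to minimize the number of participants lost to follow up".
- **Methods/design.** The timeline opens: "The trial will run for 10 months, which includes a two-month baseline period where all participants receive the 'self-serve' evidence service". It closes with "a final two-month period where both groups will receive the 'full-serve' version of SHARE".
- **Abstract, Methods/design.** The crossover is again counted inside the trial: "The trial duration will be 10 months (two-month baseline period, six-month intervention period, and two month crossover period".

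The Abstract names intention to use research evidence as the secondary outcome. Outcomes and Data management and analysis treat it as a before-and-after change, so it has one baseline and one follow-up measurement.

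**The concern.** The two statements put the only follow-up measurement of the secondary outcome at different times, and the control arm's switch to full-serve lies between them. At the earlier time the control arm has had self-serve only, which is the contrast set out in Objectives. At the later time no control organization is still on self-serve alone, and the survey can no longer estimate that contrast.

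With a single follow-up, a survey taken on the wrong side of the switch cannot be repeated. The contamination check would suffer too. According to the Discussion, the follow-up survey asks about sharing logins, and answers given at month 10 would mix sharing before the switch with sharing after it, when both arms have the same access.

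The reminders raise a smaller version of the same issue. If the survey goes out when the intervention period ends, the people chased longest answer furthest into the crossover.

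**Working it through.** **1. The plan's own figures.** The only precision figures are for the primary outcome (Statistical precision): 80% power, two-sided 0.05, SD 1.0, n = 42 per arm, m = 6 monthly measures. The formula is d = (1.960 + 0.842) × √[2(1 + (m − 1)·ICC)/(m·n)].

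| ICC | Stated | Recomputed |
|---|---|---|
| 0.2 | 0.35 | 0.353 |
| 0.3 | 0.39 | 0.395 |
| 0.5 | 0.47 | 0.467 |
| 0.7 | 0.53 | 0.529 |
| 0.8 | 0.56 | 0.558 |

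These reproduce. They concern logins over the intervention period and do not depend on the survey date. No precision figure is given for the secondary outcome.

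**2. The two dates** (durations from Methods/design).

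| Source | Calculation | Survey at | Full-serve so far, intervention arm | Full-serve so far, control arm |
|---|---|---|---|---|
| Outcomes | 2 + 6 | month 8 | 6 months | 0 months |
| Study population and recruitment | 2 + 6 + 2 | month 10 | 8 months | 2 months |

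**3. What a month-10 survey would estimate.** Let g(t) be the effect on intention of t months of full-serve. The share of the intended contrast that survives is [g(8) − g(2)] / [g(6) − g(0)]. The document gives no information on g, so only a range can be shown:
- If the effect grows in proportion to time, 8 − 2 = 6 and 6 − 0 = 6. The share is 1 and there is no dilution.
- If the effect is complete within two months, g(8) = g(2). The share is 0.
- If the effect builds early and then flattens, the share lies in between.

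**4. Illustration of the cost** (assumed: one follow-up measure, SD 1, 42 per arm, no baseline adjustment). The detectable difference at 80% power is (1.960 + 0.842) × √(2/42) = 0.61 SD. For a true difference of that size:

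| Share surviving | Difference (SD) | Power |
|---|---|---|
| 100% | 0.61 | 80% |
| 75% | 0.46 | 56% |
| 50% | 0.31 | 29% |
| 25% | 0.15 | 10% |

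**5. The reminder window.** Three weekly reminders span 21 days. If the survey opens on the last day of month 8 and access switches at once, they run to day 21 of about 61 crossover days (21/61 = 34%). That is the part of the crossover elapsed when the reminders stop, not a measure of bias. If a share p of controls answer after the switch, having moved a fraction f towards the full-serve level, the difference shrinks by p × f. The document gives neither quantity. As pure assumptions, p = 30% gives 15% with f = 0.5 and 30% with f = 1.

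**The case against.** The best defence is that the document largely settles the date itself. The recruitment sentence summarises an invitation and defers to Outcomes, which is the more specific text. Statistical precision also speaks of a six-month trial period, so completion of the trial may be loose wording for the end of the intervention. This stands: an analyst following Outcomes would use month 8. It does not remove the conflict, because both the Abstract and Methods/design count the crossover in the trial, and the recruitment text describes what organizations will be told.

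Several stronger readings are tempting but unsupported:
- A reader might infer that a month-10 survey compares full-serve with full-serve. That is true of access on the day, but cumulative exposure would still be 8 against 2 months.
- A reader might infer certain bias towards zero. Under an effect proportional to exposure there would be none. Dilution is the most plausible direction, but it is not established.
- A reader might infer that the reminders definitely run past the switch. Outcomes gives no opening or closing date, and such dates are commonly left to a full protocol. The overlap is conditional, and it is at most about three weeks for late responders only.
- A reader might take the 15% or 30% shrinkage as an estimate. Both inputs are invented. Email updates are promised only at least monthly, so a full effect within three weeks would need rapid onset. Nor does the document show that late responders differ from early ones.
- A reader might extend the point to the baseline survey. Outcomes already places it within the baseline period, when everyone has self-serve.

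**Conclusion.** The contradiction is real: month 10 in the recruitment text, month 8 in Outcomes, with the control switch between them. Month 8 is probably intended. If month 10 were followed, the sole named secondary outcome would have no self-serve-only control. The difference would most plausibly be diluted, by anything from nothing to all of it depending on how fast the effect builds, which the document cannot tell us.

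The reminder overlap is a secondary point. It rests on the survey opening at the end of month 8, the plain reading of Outcomes, and on access switching straight away.

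The primary outcome is calculated separately for each period and is not affected. Nor are the precision figures. The point is limited to the secondary outcome, but it is worth correcting before recruitment material goes out, because the single follow-up cannot be retaken.

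**What to change.** 1. In Study population and recruitment, replace the reference to trial completion with the time given in Outcomes, the end of the intervention period (month 8).
2. State a survey window such that the survey and its three reminders close before control access is switched. There are two ways to do this:
   - Open the survey a few weeks before the end of month 8. The cost is that some respondents will have had about five rather than six months of exposure.
   - Keep the opening date and switch control access only once the survey has closed. This avoids that loss but delays the start of the crossover for controls by about three weeks.
3. Record the date of each response, and use any answer given after the switch in a sensitivity analysis only.

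The cost is one corrected sentence and one scheduling decision. No sample size or precision figure changes.

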### Interventions

We will run a two-arm RCT with a 'full-serve' evidence service (SHARE) as the intervention arm and a 'self-serve' version as the control arm. The components of each version of SHARE are outlined in Table 1 and described below.

**Table 1 T1:** Components of the 'full-serve' and 'self-serve' evidence service

Evidence service components	'Full-serve' SHARE	'Self-serve' Control
1. Access to records for HIV-relevant systematic reviews*	X	X

2. Searchable database - Reviews retrievable using taxonomy of topics related to HIV/AIDS and open text search	X	

3. Email updates highlighting newly added reviews	X	

4. Access to user-friendly summaries produced by us or by others	X	

5. Links to scientific abstracts	X	X*

6. Peer-relevance assessments†	X	

7. Links to full-text (when publicly available)	X	

8. Access to worksheets that help CBOs find and use research evidence	X	X

* The 'self-serve' version will be provided as a listing of reviews grouped by year of publication with titles hyperlinked to their scientific abstract.

†Based a 5-point scale that asks how useful the reviews is and through a user-forum provided for each review record

### Intervention arm: 'full serve' evidence service

Organizations allocated to this study arm will receive access to a 'full-serve' version of SHARE, which provides:

1. an online searchable database of HIV-relevant systematic reviews (retrievable based on a taxonomy of topics related to HIV/AIDS and open text search - see Additional file 1: Appendix 1 for the taxonomy of topics);

2. periodic email updates (at least one per month), which will profile the types of new reviews recently added to the database (*e.g.*, the number of Cochrane reviews) and provide a brief overview of the range of topics addressed by the new reviews;

3. access to user-friendly summaries produced by us or by others (when available);

4. links to scientific abstracts;

5. peer relevance assessments, which involves periodic requests (contained in the single record for each review) to complete a brief assessment of how useful the information in the newly added review is (one question with a five-point scale - see Additional file 2: Appendix 2 for additional details) with the average score posted once an assessment is completed;

6. an interface for participants to leave comments (up to 250 characters in length) in the records of systematic reviews in the database (*e.g.*, if a participant wants to leave a comment indicating the review was useful and why);

7. links to full-text articles (when publicly available); and

8. access to worksheets that help CBOs find and use research evidence

To provide access to user-friendly summaries (see component three above) we will provide links to user-friendly summaries produced by nine groups (when available) from around the world: Australasian Cochrane Centre (AAC) Policy Liaison Initiative, Database of Abstracts of Review of Effects (DARE), Effective Healthcare Research Programme Consortium, Evidence AID, Health Knowledge Network, Health-Evidence.ca, Reproductive Health Library, Rx for Change, and Supporting Policy Relevant Reviews and Trials (SUPPORT)[18,26-34].

### Control arm

Organizations allocated to the control group will only be provided website access to a listing of systematic reviews that are organized by year of publication with links to the record on PubMed (or another publicly available source when not available on PubMed) and access to worksheets that help CBOs find and use research evidence.

